## 10 ETHICAL CONSIDERATIONS

### 10.1 Regulation statement

All experiments and handling of samples will be performed according to the latest version of the declaration of Helsinki (last amended at the 59th WMA General Assembly, Seoul, Korea, October 2008), the Medical Research Involving Human Subjects Act (WMO), and Good Clinical Practice.

### 10.2 Recruitment and consent

Healthy volunteers will be recruited by advertisements (e.g. flyers, posters) in Nijmegen, on bulletin boards at the university, via online bulletin boards and through presentations at the university. In addition, information about this study will be provided to participants of previous studies (e.g. the 500FG project) at our department that have given permission to be approached for future studies. Written information about the study will be provided and subjects have the opportunity to ask questions to the investigator. If subjects want to participate in the study, the main investigator will discuss the study with them and subjects can ask questions if they have any. In addition, an independent physician could provide answers to questions subjects might have. If subjects would like to participate in the study and they meet all the in- and exclusion criteria, informed consent will be signed and upcoming visits will be planned. At least one day will be taken into account before informed consent can be given. Please find attached as separate documents the patient information and informed consent form.

### 10.3 Benefits and risks assessment, group relatedness

The study population consists of healthy adults. Apart from protection against extrapulmonary infection with *Mycobacterium tuberculosis* and against leprosy, there are no expected benefits for participants in the study. However, findings may show new mechanisms responsible for the non-specific effects of vaccination and this may lead to novel strategies to optimize vaccination programs.

The risks to the subjects in this study are minimal. Potential risks include only the side effects of the vaccine, of which localized skin reactions are most common. The local reaction after BCG vaccination is usually mild and self-limiting. Less common are fever and headache after vaccination and if they occur they are typically mild. Enlargement of the axillary lymph nodes may occasionally occur after vaccination but will usually regress spontaneously after a few months.

No risks other than local hematoma and minor pain are related to venous puncture. Risks will be minimized since venipuncture will be performed by experienced personnel.

In conclusion, the potential risk and burden are proportional to the potential value of this study.

#### **10.4 Compensation for injury**

The sponsor/investigator has a liability insurance which is in accordance with article 7 of the WMO.

The sponsor (also) has an insurance which is in accordance with the legal requirements in the Netherlands (Article 7 WMO). This insurance provides cover for damage to research subjects through injury or death caused by the study.

The insurance applies to the damage that becomes apparent during the study or within 4 years after the end of the study.

#### **10.5 Incentives**

Participants in this study will receive 150 Euro (i.e. hundred fifty Euro) as compensation for the time spent in the hospital for study procedures. The BCG vaccine (about 35 euro) is given to the subjects free of charge and might benefit them in the future. A proportional share of the total fee will be given when a subject ends participation before the end of the study. When the reason for withdrawal is because of medical issues, the entire fee will be given.

## **11. ADMINISTRATIVE ASPECTS, MONITORING AND PUBLICATION**

### **11.1 Handling and storage of data and documents**

Data will be handled coded and confidentially. The main investigator will code samples and only he/she and the PI will have access to the data. The code list linking the subjects to the coded data/materials will be stored by the main investigator. The code will consist of the study code followed by SxVx, where 'S' will indicate the subject number and V the different time points. All study materials (e.g. supernatants, lysed cells, plasma, stool and oral samples) will be stored according to Good Clinical practice and in a completely coded way up to 15 years. Both the main investigator and the PI have access to stored material.

This study follows a systems biology approach. This means that there is the possibility to produce large datasets. The study materials will be stored up to 15 years in order to perform experiments on innate immune memory with the current but also with potentially new techniques. The purpose of this is to facilitate all analyses performed in order to elucidate the underlying mechanisms of trained immunity; such as measuring additional pro-inflammatory cytokines, RNA transcription etcetera. Hence, there will be a direct link with the current research proposal.

All materials will be stored in a locked freezer at the department of Internal Medicine of the Radboudumc. The materials will be managed by the Principal Investigator (PI), professor [name]. The PI is responsible for all materials and his permission is needed when there is a request for material transfer, which will be in an anonymous form. Assessment by an accredited medical research ethics committee is required before materials will be used for research that has no connections with the current subject of research and/or research in which there is a possibility to encounter ancillary findings. Volunteers will be asked for their permission to store and analyse materials after the indicated study period on the informed consent form. On the same form, volunteers are also asked for their permission to be approached after the study period for future studies or follow-up.

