###### **b. Cytokine Measurements**

Cytokine production will be assessed with ELISA after 24h (IL-6, TNF $\alpha$ , IL1- $\beta$ ) or 7 days (IFN $\gamma$ , IL-17, IL-22) incubation. The cytokine production at two different time points after vaccination will be compared with the response before vaccination.

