###### **c. Immunophenotyping**

Immunophenotyping of cell subpopulations using myeloid cell and lymphocyte protocols will be done using FACS analysis.

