## **6) Skin inflammation at vaccination site**

The vaccination site will be examined two weeks after BCG vaccination. A picture will be taken and scar size and the presence of local inflammation will be documented by an independent researcher.

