### **Invasive procedures to be performed:**

Day 0 (visit 1): vena puncture: 2.5 ml PaxGene tube, 50 ml EDTA blood, 8 ml serum  
vaccination with BCG vaccine.

Day 14 (visit 2): vena puncture: 2.5 ml PaxGene tube, 50 ml EDTA blood, 8 ml serum

Month 3 (visit 3): vena puncture: 2.5 ml PaxGene tube, 50 ml EDTA blood, 8 ml serum

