### **Laboratory techniques to be performed:**

**Stimulation and cytokine assays:** At all time points PBMC isolation will be performed and monocytes will be *ex vivo* stimulated with various pathogens. Cytokine production will be assessed after 24 hours and after 7 days with ELISA technique. Cytokine levels before and after vaccination will be compared. Immunophenotyping will be done using FACS analysis.

**Genomics:** At the first visit 3 ml of blood for DNA isolation of healthy volunteers will be stored.

**Microbiome:** Samples will be analysed by shotgun metagenome sequencing.

**Epigenomics, transcriptomics metabolomics:** Supernatant and cell lysates will be stored for epigenomics, transcriptomics and metabolomics studies.

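### The only sample code the protocol specifies shows the visit, and no masking of assay readers to before/after status is described

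*Protocol*

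**What the plan says.** Section 11.1 (Handling and storage of data and documents) sets the code: "The code will consist of the study code followed by SxVx, where 'S' will indicate the subject number and V the different time points". It adds "The main investigator will code samples and only he/she and the PI will have access to the data". Of the principal investigator it says "his permission is needed when there is a request for material transfer, which will be in an anonymous form". It names supernatants, lysed cells, plasma, stool and oral samples among the materials stored in coded form. No other sample code appears in the protocol.

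Section 3 and section 7.1.1 (Stimulation Assays) place the first blood draw before vaccination. Section 7.2 numbers the visits: visit 1 on day 0, visit 2 on day 14, visit 3 at month 3. All participants receive BCG.

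The main cytokine comparison is within person (section 7.1.1, Cytokine Measurements): "The cytokine production at two different time points after vaccination will be compared with the response before vaccination". Section 9.1 tests it with the Wilcoxon signed rank test at the 0.05 level. Cell subpopulations are also a main parameter: "Immunophenotyping of cell subpopulations using myeloid cell and lymphocyte protocols will be done using FACS analysis".

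The protocol does not mention masking laboratory staff to time point, a second label, or randomised plate order.

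**The concern.** In a trial with a parallel control arm, a visit number on the label would still hide the treatment. Here there is one arm, and the contrast under test is visit 1 against visits 2 and 3. A code that carries the visit shows that contrast without any key.

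The work is done in the group's own laboratory (section 3.5), and the introduction and section 6.3 state a directional expectation that responses are enhanced after BCG. Where a read-out leaves room for judgement, such as placing FACS gates, repeating a run or excluding a value, a reader who knows the visit may treat the two sides differently without intending to. With no control arm, that difference adds to the before/after change and cannot be removed afterwards. A later analysis plan cannot re-mask samples that have already been read.

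**Working it through.** **Does the code disclose the contrast?**

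1. The code contains V, the time point (section 11.1).
2. Visit 1 is day 0 and the blood is drawn before vaccination (sections 3, 7.1.1, 7.2). So V1 means before BCG.
3. Visits 2 and 3 are day 14 and month 3. So V2 and V3 mean after BCG.
4. The test in sections 7.1.1 and 9.1 compares V1 with V2 and with V3.

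The V digit is therefore enough to place a sample on one side of the tested contrast.

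**Which analyses are exposed?** Let a person's change be d_i + b, where d_i is the true change and b a handling shift common to all samples taken after vaccination.

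- *Before/after test (section 9.1):* the mean change becomes mean(d_i) + b, so b enters in full.
- *Host-factor associations (primary objective, section 2):* if the change is regressed on sex, age, genotype or microbiome, a constant b goes into the intercept and leaves the slopes unchanged. Only a shift that varies between persons, or scales with the response, reaches them. The exposure is indirect.
- *Germline genotyping:* DNA comes from blood taken at the first visit and has no before/after contrast. It is not exposed.

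**Illustration of sensitivity.** The protocol gives no SD, effect size or power figure (section 4.4), so it has no figure of its own to reproduce. Inputs: n = 300 pairs (section 4.4), two-sided level 0.05 (section 9.1), and an assumed shift s of 0.05, 0.10 or 0.15 SD of the paired difference. The shifts have no source in the documents.

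- Standard error of the mean paired change, in SD units: 1/√300 = 0.0577.
- Rejection probability with no BCG effect: Φ(s√300 − 1.96) + Φ(−s√300 − 1.96).

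| Assumed shift s | s√300 | Rejection probability |
|---|---|---|
| 0.05 | 0.866 | 0.139 |
| 0.10 | 1.732 | 0.410 |
| 0.15 | 2.598 | 0.738 |

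This is a normal approximation for a mean. The planned Wilcoxon test would be slightly less sensitive if the differences are normal. The table shows that 300 pairs make small systematic shifts detectable. It does not show that the label produces a shift of any given size.

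**The case against.** Section 11.1 is about confidentiality and storage. It does not say that SxVx is on every assay plate, FACS tube or transferred aliquot, and a laboratory manual that is not shown may set aliquot labels. This stands. A reader might infer that everyone who handles a sample sees the visit, but the text does not support that. It does, however, specify only this one code and no masking step. The promise of anonymous transfer concerns identity, and it is not said whether the visit digit is removed.

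A reader might also infer that no laboratory blind can hold. That does not follow. Nothing in section 11.1 forbids recoding, and supernatants and lysates are stored (sections 7.2 and 11.1), so they can be relabelled before read-out. Nor is a promised blind contradicted, because none is promised. The reference in section 8.2.2 to breaking a randomization code has no counterpart in a study where nothing is randomised.

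The label is not the only source of knowledge. Section 7.2 states "At all time points PBMC isolation will be performed and monocytes will be" stimulated with pathogens, so staff at that step may know the visit from the clinic schedule. This stands and limits what recoding can achieve.

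It is tempting to contrast the laboratory work with the vaccination site, where section 7.1.2 says "scar size and the presence of local inflammation will be documented by an independent researcher", and to conclude that the plan protects a lesser endpoint but not the main ones. The comparison fails. The site is examined two weeks after vaccination, so there is no before/after contrast to mask, and an independent researcher is not necessarily unaware of the visit.

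Finally, the protocol describes no gating, repeat or exclusion procedure, so the room for judgement is inferred from the kind of assay. The assumed shifts are not evidence about this laboratory.

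**Conclusion.** The concern holds in a limited form. The only code specified discloses before/after status, and no masking of assay readers is described. Before/after read-outs may therefore be unmasked unless samples are recoded. The exposure falls on the overall before/after comparison, which section 9.1 treats as a first step. It reaches the host-factor associations of the primary objective only indirectly, and genotyping not at all.

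The size of any bias is unknown. The range of about 14% to 74% false-positive tests rests on assumed shifts of 0.05 to 0.15 SD of the paired difference, 300 complete pairs and a normal approximation. The conclusion also assumes that assay readers see the SxVx code, which the protocol neither states nor excludes. This is a cheap improvement to a stated rule and not a flaw that invalidates the design.

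**What to change.** Amend section 11.1 so that:

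- SxVx stays in the code list held by the main investigator;
- stored supernatants, lysates and FACS files carry a random number that does not show the visit;
- all three visits of a person are assayed on one plate, in random order;
- the visit key is released only after gating, repeats and exclusions are locked.

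State also that isolation and stimulation of fresh cells can be masked only in part.

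The cost is an amended rule, a relabelling list and a small risk of label mix-ups, which a barcode log would cover. Running a person's visits together means that the read-out waits for the month 3 sample. No extra staff, assays or participant procedures are needed.

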### **11.2 Monitoring and Quality Assurance**

Monitoring of this study will be done in accordance with the monitoring plan, which is made in collaboration with the Clinical Research Centre Nijmegen.

### **11.3 Amendments**

Amendments are changes made to the research after a favourable opinion by the accredited METC has been given. All amendments will be notified to the METC that gave a favourable opinion.

### **11.4 Annual progress report**

The sponsor/investigator will submit a summary of the progress of the trial to the accredited METC once a year. Information will be provided on the date of inclusion of the first subject, numbers of subjects included and numbers of subjects that have completed the trial, serious adverse events/serious adverse reactions, other problems, and amendments.

### **11.5 Temporary halt and (prematurely) end of study report**

The investigator/sponsor will notify the accredited METC of the end of the study within a period of 8 weeks. The end of the study is defined as the last patient's last visit.

The sponsor will notify the METC immediately of a temporary halt of the study, including the reason of such an action.

In case the study is ended prematurely, the sponsor will notify the accredited METC within 15 days, including the reasons for the premature termination.

Within one year after the end of the study, the investigator/sponsor will submit a final study report with the results of the study, including any publications/abstracts of the study, to the accredited METC.

### **11.6 Public disclosure and publication policy**

The study results, both positive and negative, will be submitted for publication to peer reviewed journals. The investigators will hold final responsibility for the decision to submit publications.

## 12. STRUCTURED RISK ANALYSIS

### 12.1 Synthesis

The risks for participation in this study are very low. BCG vaccine is the most widely used vaccine in the world, being part of vaccination policies in many countries. The side effects of the vaccine are very well known and the common side effects are minor and almost always self-limiting. Major side effects are very rare in healthy people (see also summary of product characteristics). The BCG vaccine which will be used in the study has been selected by the RIVM for use in the Netherlands (under approval of the Ministry of VWS) and is delivered by InterVax (Toronto, Canada) to the RIVM. The vaccine is produced by BB-NCIPD Ltd (Sofia, Bulgaria) and is registered in Bulgaria. The vaccine has been recently approved by the CCMO for use in another study performed by our department (NL56222.01 9.15).

Because of the negligible risks for the healthy volunteers included in this study, we consider this trial a non-medicinal product trial.

